**Fig. 1 Fig1:**
[figure not shown]
Standard protocol items recommendations for intervention trials (SPIRIT): Schedule of enrolment, intervention, and assessments for the SHAPE trial

### Sample size

The sample size calculation is based on the approach outlined in Lohr et al. [35] and the aim of detecting a standardised mean difference of 0.4 in the General Self-Efficacy Scale (GSES) between the intervention and control arms of the trial, with 90% power at the 5% significance level. An effect size (Cohen’s D) of 0.4 is a commonly used threshold for clinical meaningfulness [36]. A standard sample size calculation suggests that 268 participants would be required (134 participants per arm). Including in the analysis covariates that are predictive of the outcome will increase the precision of the effect estimate and hence the statistical power. Assuming a coefficient of determination R2 of 0.25 for the regression of the outcome on baseline variables, the required total sample size is reduced to 201 [37].

Due to the potential for a clustering effect in the intervention because participants are attending group sessions where the outcomes for individuals nested within the same educational groups [WS8] are likely to be more similar than the outcomes for individuals within different groups, the variance in the intervention arm will be inflated. We assume a residual intra-cluster correlation coefficient (ICC) of 0.1. We plan for group sizes of 8 in the intervention arm and an allocation ratio of 2:1 (i.e. 67% of participants will be allocated to the treatment arm). Assuming 25% attrition we anticipate an average number of 6 participants within each cluster contributing data for analysis. Given this plan, and allowing for attrition, we will need to recruit a total of 246 participants to the intervention arm and 123 participants to the TAU arm in order to provide sufficient power for the primary analysis. Harmonising to a fixed block size we will recruit 248 participants to the treatment arm and 124 participants to the control arm, i.e. a total of 372 participants. Additional allowance for varying group sizes is not necessary if the coefficient of variation in cluster sizes is smaller than 0.23 [38], which we expect to be the case in this study design.

### Recruiting centres

Stavanger University Hospital (SUH) and Norwegian National Advisory Unit on Ageing and Health in Norway (AH), the University of Exeter and partner National Health Service (NHS) Trust(s) in the UK, the University of New South Wales with Prince of Wales Hospital (UNSW) and Dementia Australia as partners will all act as recruiting centres.

### Planned recruitment rate

Across all four sites combined, we will recruit a total of 372 participants to the study. The recruitment will happen in blocks of 12 participants at each site, of which 8 will be randomised to the SHAPE intervention and 4 to TAU. The planned distribution among the centres is 84 participants at Exeter, 96 at A&H, 108 at SUH and 84 at UNSW.

Month 1 will be spent recruiting the first blocks of participants, who will have their baseline visits in the first 2 weeks of month 2, with a maximum of 2 baseline interviews per day at each centre. Following this we will randomise consenting participants, and inform them of their allocation and for those in the intervention arm the start date of the course. Start-up of the first course groups will be in month 3. Further recruitment will happen concurrently, and we anticipate that we will have enough participants to start up at least one new course group at each centre every 1.5 months, meaning that recruitment will be completed in 13 months, and the last course groups will start in month 15.

### Randomisation

When recruitment reaches a group target of 12 consented pairs of participant and carer partners at a site we will proceed to randomisation. A computer-generated randomisation sequence will be used to assign the participant pairs in each site to the intervention and control arms. A block randomisation scheme will be implemented to ensure an appropriate ratio in the number of participant pairs allocated to each trial arm, stratified by group delivery site. The allocation sequence will be concealed from researchers (outcome assessors) using an online central randomisation service set up and maintained by the Exeter Clinical Trials Unit (UKCRC Registration ID 65). Group facilitators and pairs of participant and care partners will not be blinded.

The participants and their care partners will receive an email and letter indicating the result of randomisation. Participants allocated to the intervention arm will be sent details of the group sessions and will be contacted by their Lead Facilitator before the first group session, and their care partner will receive a link to the online e-learning platform.

### Blinding

Quantitative data will be collected by a researcher blind to the participants’ allocation (intervention vs TAU).

### Outcome and study eligibility measures

All quantitative outcome measures will be assessed prior to randomisation (baseline), after the intervention (follow-up 1) and then 6 months after follow-up 1 (follow-up 2). The assessments will consist of questionnaires using standardised, evidence-based scales and other information obtained from the participant and appointed care partner. The interviews will be conducted with the participant and care partner, both together and separately. Participant and care partner demographic details will be collected.

The primary outcome in the SHAPE trial is self-efficacy measured by the General Self-Efficacy Scale (GSES) [39]. The secondary outcome measures include cognition assessed with the Mini Mental State Examination (MMSE) [40], which is also used to check eligibility, depressive symptoms measured by the Cornell Scale for Depression in Dementia (CSDD) [41], quality of life and well-being measured by the Dementia Quality of Life Scale (DEMQOL) [42], health-related quality of life measured by EQ-5D-5L [43], neuropsychiatric symptoms measured by the Neuropsychiatric Inventory Questionnaire (NPI-Q) [44], health behaviour changes measured by the SHAPE research team health reporting form, use of support services measured by the Client Services Receipt Inventory (CSRI) [45], carer stress measured by the Relative‘s Stress Scale (RSS) [48], carer sense of competence measured by the Short Sense of Competence Questionnaire (SSCQ) Short version [49], and knowledge about dementia measured by the Dementia Knowledge Assessment Scale (DKAS) [50]. We will use the Clinical Dementia Rating Scale (CDR) [39] to measure level of dementia and to measure functional changes in the participants we will use the Functional Activities Questionnaire (FAQ) [40]. A full description of the primary and secondary outcomes and screening instruments is provided in Table 2.

**Table 2 Tab2:** Description of measures

Measures	What does the tool measure	Informant	Tool characteristics and psychometric properties
CDR [49]	Diagnostic criteria	Care partner	Assesses six domains of cognitive and functional performance: memory, orientation, judgment & problem solving, community affairs, home & hobbies, and personal care. 0 = no cognitive impairment, 0.5 = questionable or very mild dementia, 1, 2 and 3 for mild, moderate and severe dementia. Scores in each of these are combined to obtain a composite score ranging from 0 (none) through 3 (severe).
FAQ [50]	Functional changes	Care partner	10-item scale measuring instrumental activities of daily living. The score range for each item is 0–3, with higher scores indicate greater impairment; 0 = normal or never did but could do now; 1 = has difficulty but does by self or never did but would have difficulty now; 2 = requires assistance; 3 = dependent.
MMSE [40]	Cognition	Participant	30-point questionnaire, with items assessing orientation, attention, immediate and short-term recall, language, and the ability to follow simple verbal and written commands. Lower scores indicating more severe cognitive problems.
GSES [39]	Self-efficacy *Primary outcome*	Participant	10-item psychometric scale designed to assess a person’s sense of competence for dealing effectively with a variety of stressful situations. Responses are rated on a 4-point Likert scale. Total score ranges from 1o to 40, with higher values indicating greater self-efficacy.
CSDD [41]	Depressive symptoms	Participant and care partner separately	Based on impressions from interviews with the person with dementia and their care partner, the final ratings of the CSDD items represent the rater’s clinical impression rather than the responses of the care partner or the person with dementia. The scale consists of 19 items that ranges from 0 (absent) to 2 (severe). Total score ranges from 0 to 38, with higher values indicating more depressive symptoms.
DEMQOL [42]	Quality of life and well-being	Participant and care partner separately	The measure consists of two questionnaires. DEMQOL, conducted with person with dementia is a 28-item interviewer- administered questionnaire with the score range of 28 to 112. DEMQOL-Proxy is a 31-item interviewer-administered questionnaire answered by a care partner with a score range of 31 to 124. The DEMQOL-Proxy is also validated as a method for calculating QALYs for health economic analysis.
EQ-5D-5L [43]	Health-related quality of life	Participant and care partner separately	Participant and their care partner indicate the participant’s health state across five dimensions: mobility, self-care, usual activities, pain/discomfort and anxiety/depression. Each dimension has 5 levels: no problems, slight problems, moderate problems, severe problems and extreme problems. Additionally, the participant’s self-rated health is measured on a vertical, visual analogue scale, where 0 represents ‘worst imaginable health state’ and 100 represents ‘best imaginable health state’.
NPI-Q [44]	Neuropsychiatric symptoms	Care partner	12-item questionnaire developed to assess behavioural disturbances in people with dementia. NPI-Q is a validated structured interview assessment with a care partner. Scores are entered for the frequency and severity of each symptom over the last four weeks, and subsequently multiplied into a symptom score. The total possible maximum score is 144. A higher score reflects increased frequency and severity of the disturbances.
Self-rated Health Behaviour Change	Health behaviour changes	Participant and care partner separately	The SHAPE research team will create a health reporting form based on the SHAPE intervention that asks about specific health-related change that occurred during each time period. Data from self- and family report.
CSRI [45]	Use of support services	Participant and care partner together	Used to estimate the cost of the participant’s service package and of support services for the care partner. Information collected: participant’s use of hospital, community-based and day services, participant’s mental health medications, care partner’s use of support services and mental health medications. Questions cover a retrospective period of 3 months.
RSS [46]	Carer stress	Care partner	15-item, 5-scale self-report measure designed to assess the degree of distress and social upset experienced by a relative as the result of caring for a person with physical and/or behavioural difficulties.
SSCQ [47]	Carer sense of competence	Care partner	7-item questionnaire covering 3 domains: consequences of involvement in care for the personal life of the care partner, satisfaction with one’s own performance as a care partner, and satisfaction with the person with dementia as a recipient of care.
DKAS [48]	Knowledge about dementia	Care partner	25-item scale measuring dementia knowledge across four domains: causes and characteristics, communication and behaviour, care considerations, and risks and health promotion.

CDR: Clinical Dementia Rating Scale, FAQ: Functional Activities Questionnaire, MMSE: Mini Mental State Examination, GSES: General Self-Efficacy Scale, CSDD: Cornell Scale for Depression in Dementia, DEMQOL: Dementia Quality of Life Scale, NPI-Q: Neuropsychiatric Inventory Questionnaire, CSRI: Client Service Receipt Inventory: RSS: Relative‘s Stress Scale, SSCQ: Short Sense of Competence Questionnaire, DKAS: Dementia Knowledge Assessment Scale

### Economic evaluation

For the economic evaluation, there will be two co-primary outcomes: self-efficacy (GSES) [39] and QALY gain (calculated from EQ-5D-5L self-report; societal weights) [43]. Secondary outcomes will be QALY gain from DEMQOL self-report [51], care partners’ QALY gain (calculated from carer-reported EQ-5D-5L), CSDD [41], and carer stress (RSS) [46]. Two perspectives will be employed: health and social care system, and societal (including costs of unpaid care).

Costs of the self-management intervention (e.g. staff costs, room hire and materials) will be collected on pro-formas devised for the study; costs of the e-learning course for care partners will be collected from the project team. We will calculate incremental cost-effectiveness ratios (ICER) as the difference in costs between SHAPE and TAU (either service-related or societal, depending on perspective) over the difference in outcomes between groups, for each outcome in turn. Service-related costs will be based on (i) participant-with-dementia service costs; and (ii) costs of participants’ and care partners’ service use. In addition, an ICER will be calculated from participant-plus-carer costs and combined participant and care partner QALY (calculated from EQ-5D). Cost-effectiveness analyses will be conducted using a combination of bootstrap sampling and cost and outcome regressions taking into account clustering, correlations between costs and outcomes, and skewed dependent variables. Regressions will include treatment allocation; baseline scores of the dependent variable (e.g. utility, GSES, costs and other baseline variables as relevant). Sensitivity analyses will explore impact on findings of changes in key cost and outcome assumptions. We will calculate net monetary benefit and construct cost-effectiveness acceptability curves to explore the likelihood of cost-effectiveness over a range of willingness-to-pay values, taking into account decision and sampling uncertainty [52, 53].

### Qualitative evaluation

Qualitative outcome will be obtained during the intervention and immediately after group completion, using direct observations of participants and focus groups with group facilitators. The qualitative evaluation is designed to develop a deeper understanding of and insight into the intervention to i) provide recommendations for future work and ii) explore the impact of the intervention on self-efficacy and wellbeing.

#### Group observations

To study the process of engagement in the group sessions, we will observe 5 groups (3 in Norway, 1 in UK and 1 in AU), each consisting of up to 8 participants (*n* = 40) over the duration of the course (10 weeks). We will use a moderate participant observation method, where the researchers are present and identifiable, without engaging in any form of interaction with the participants [54]. The observations will be carried out on study commencement, by an observation team with a minimum of two researchers with different backgrounds. We will develop an observational protocol that includes a range of pre-selected topics, including (1) in-session behaviour, (2) participant engagement, (3) social interaction within the group, (4) peer support and (5) change in perceptions of living with dementia. The field notes will be transferred to word documents for analysis.

#### Focus groups

To identify promoting and hindering factors affecting the SHAPE intervention, focus groups involving the group facilitators (*n* = 4–8) will be conducted in all sites (*n* = 5, i.e. 3 in Norway, 1 in UK and 1 in AU). The focus groups will be led by an experienced researcher (moderator), and a co- moderator will make notes on observations and impressions during the focus group discussions. A semi-structured topic guide, which will be revised iteratively allowing the main issues identified by participants to be explored in depth, will guide the discussions (see Additional file 1). The focus groups will be recorded and transcribed verbatim; observations and impressions will be noted at the end of each group.

### Intervention fidelity

To monitor intervention fidelity, group facilitators will complete checklists of topics covered in each session and outline any deviations from the session plans. Participants’ attendance at the sessions will be recorded. If participants do not meet up for a session, the group facilitators will follow-up with a phone call.

### Participant selection: inclusion, exclusion and withdrawal criteria

#### Inclusion criteria

Diagnosis of dementia according to the ICD-10 classification [55] or the Diagnostic and Statistical Manual of Mental Disorders (DSM) IV or V [56]65 years of age or olderMild to moderate dementia, defined as MMSE ≥18Ability to read and writeHearing and vision that are sufficiently good to work in a group settingCapacity to give consent for participation in the studyProficient in the language in which the intervention is providedCare partner willing to participate

#### Exclusion criteria

A diagnosis of alcohol or drug abuseLewy body dementia, Fronto-temporal lobar degeneration or Semantic dementiaA limited life expectancy due to any terminal disease or other serious illness, other than dementiaChemotherapy or radiation treatment ongoing at enrolmentCurrently participating in another health promotion or self-management group

### Withdrawal criteria

Individual participants can withdraw from the study at any time, without giving a reason.

### Enrolment procedure

Details of enrolment, how the participants will be informed whether they have been allocated into the intervention or TAU, and enrolment in the e-learning program are shown in Fig. 2. Information will be given to primary care services, including general practitioners (GP) offices; memory clinics, user organisations and social media through flyers in the areas of the individual study sites.

**Fig. 2 Fig2:**
[figure not shown]
Enrolment process

### Safety reports of serious adverse events (SAE)

Fatal and life-threatening events (otherwise known as Serious Adverse Events) experienced by participants while participating in the study are unlikely to be caused by participation in this trial; however, they will be recorded. SAE reporting will be done according to the requirements of the National Research Ethics Service (NRES) in each individual country. The site PI will inform trial managers and the sponsor of local procedures and ensure that these are followed at each site. SAEs will also be reported to the sponsor and Independent Data Monitoring Committee (IDMC) every 6 months, unless more frequent reporting is requested. PIs will also ensure that AEs are recorded, but there is no requirement to report these to the sponsor or regulatory bodies unless requested.

The IDMC will consist of an independent statistician (Chair), a consumer/user representative and a researcher. There will also be a trial representative on the committee. The IDMC will meet every 6 months and if necessary in response to any serious untoward incidents. The IDMC will be responsible for monitoring serious adverse effects, protocol violations and any risks emerging from the trial.

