### Assessment and management of risk

This is a low-risk, non-pharmacological trial [32]; in such trials, certain adverse events are not required to be reported, but should be recorded. Minimal risk of psychological stress may occur as a result of assessments (e.g. completing a depression scale). Should psychological distress occur, the research team will provide participants with information about local resources that will assist with their distress.

If a participant is hospitalised during the intervention, this will be recorded. No deaths are anticipated as a result of the intervention. However, if a participant dies during the trial period, follow-up assessments that include the care partner will be discontinued.

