### The SHAPE intervention

The SHAPE intervention is based on the Corbin and Strauss Trajectory Model [34], and combines approaches of self-management, health promotion, and e-learning. The intervention is designed to develop self-management skills in areas including decision-making, symptom management and social interaction and to provide information on the disease process and the development of healthy behaviours in a supportive learning environment. The intervention comprises ten weekly 2-h group sessions for persons with dementia, where each session is led by two trained facilitators at each study site. The group facilitators will have professional clinical training e.g. nursing, occupational therapy, and psychology and have experience of working with people with dementia. For the care partners involved as study partners, the same material presented in the 10-week SHAPE course for people with dementia, plus some additional material and signposting to support them in their role, will be delivered through an online e-learning platform. Key themes of the intervention will include positive actions to improve and maintain health, how to talk about the impact of the disease on the life of the person with dementia, addressing the fear of losing independence and how to tackle and solve other sensitive issues (Table 1).

**Table 1 Tab1:** Key themes covered in the intervention

Sessions	Topic
Session 1	Orientation to the course
Session 2	Healthy lifestyle, doctor’s visits and use of medication
Session 3	Healthy eating, diet and nutrition
Session 4	Staying safe
Session 5	Exercising body and brain
Session 6	Activities, interests and learning
Session 7	Managing memory difficulties
Session 8	Adapting and coping
Session 9	Relationships and communication
Session 10	Planning for the future

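### SAEs are defined as fatal or life-threatening events only, and other hospitalisations have no stated route to the IDMC on equal terms in both arms through follow-up 2

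*Protocol article*

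**What the plan says.** The section *Safety reports of serious adverse events (SAE)* defines the reportable class as "Fatal and life-threatening events (otherwise known as Serious Adverse Events) experienced by participants while participating in the study". Hospitalisation is not named there. The onward flow is that "SAEs will also be reported to the sponsor and Independent Data Monitoring Committee (IDMC) every 6 months", or more often if asked. National rules also apply: "SAE reporting will be done according to the requirements of the National Research Ethics Service (NRES) in each individual country". For everything below the serious threshold, "PIs will also ensure that AEs are recorded, but there is no requirement to report these to the sponsor or regulatory bodies unless requested". The same section gives the IDMC a remit that covers serious effects, protocol violations and any emerging risk.

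Hospitalisation appears only under *Assessment and management of risk*: "If a participant is hospitalised during the intervention, this will be recorded". That section gives no onward reporting.

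Three other sections bear on the point.

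- *The SHAPE intervention*: "The intervention comprises ten weekly 2-h group sessions for persons with dementia".
- *Outcome and study eligibility measures*: outcomes are "assessed prior to randomisation (baseline), after the intervention (follow-up 1) and then 6 months after follow-up 1". Table 2 in that section lists the Client Service Receipt Inventory (CSRI), which asks about hospital use over the preceding 3 months.
- *Blinding*: quantitative data are collected by a researcher who does not know the allocation.

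**The concern.** The two safety sections do not fit together. One sets a narrow definition of what is serious and sends only that class to the IDMC as routine. The other recognises hospitalisation as worth recording, but ties it to the intervention and sends it nowhere. The committee's remit is therefore wider than the data it is stated to receive.

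There is also a question of balance between arms. TAU participants have no intervention period in the literal sense, so the rule is undefined for 124 of the 372 planned participants. Under *Intervention fidelity*, attendance is recorded and facilitators telephone anyone who misses a session. That contact exists only in the SHAPE arm, so an admission could be noticed there and missed in TAU.

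What is at stake is the by-arm comparison of admissions. Participants are aged 65 or older and have dementia, so admissions for unrelated causes can be expected in both arms. They can be interpreted only if they are counted in the same way in each. Uneven detection could make the intervention look less safe than it is, and a window that closes with the course would miss anything later.

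**Working it through.** The plan gives no rate for serious events or hospitalisations, so there is no stated figure to reproduce. The check has two parts: which events reach the IDMC, and how much of follow-up each recording route covers.

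**1. Which events reach the IDMC, as written**

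| Event | Recorded in | Time limit stated | Stated route to IDMC |
|---|---|---|---|
| Fatal or life-threatening | both arms | none (all of participation) | yes, every 6 months |
| Other hospitalisation, under the risk section | SHAPE; TAU undefined | intervention period | none |
| Other adverse event, recorded by site PIs | no arm limit | none | none; to sponsor or regulators only on request |
| Hospital use from CSRI | both arms | 3-month recall at each visit | none |

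The gap is in the last three rows. Admissions may be recorded there, but nothing sends them to the committee.

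**2. Share of follow-up covered**

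Inputs: course 10 weeks (*The SHAPE intervention*); follow-up 2 six months after follow-up 1, taken as 26 weeks (*Outcome and study eligibility measures*); CSRI recall 3 months, taken as 13 weeks (Table 2). Two assumptions are added. The lag L from baseline to course start is 0 to 6 weeks, because *Planned recruitment rate* puts baseline visits early in month 2 and the first courses in month 3. Follow-up 1 is taken to fall at the end of the course.

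- Total follow-up: T = L + 10 + 26.
- Share covered by the hospitalisation rule: 10 / T.
- Share covered by CSRI recall at the two follow-ups: [min(13, L + 10) + 13] / T.

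| L (weeks) | T (weeks) | Hospitalisation rule | CSRI recall |
|---|---|---|---|
| 0 | 36 | 10/36 = 28% | (10 + 13)/36 = 64% |
| 2 | 38 | 10/38 = 26% | (12 + 13)/38 = 66% |
| 4 | 40 | 10/40 = 25% | (13 + 13)/40 = 65% |
| 6 | 42 | 10/42 = 24% | (13 + 13)/42 = 62% |

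The hospitalisation rule covers 24% to 28% of follow-up in the SHAPE arm and an undefined share in TAU. The CSRI covers 62% to 66% in both arms. Its main gap is the first 26 − 13 = 13 weeks after follow-up 1. If L exceeds 3 weeks there is a second, smaller gap straight after baseline, of L + 10 − 13 weeks; this is 3 weeks when L = 6.

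**The case against.** The case for leaving the text alone has real substance.

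- **Serious events as defined are covered.** The definition applies to all participants throughout the study, and those events go to the IDMC every 6 months. A reader might infer that the committee cannot compare serious events between arms. The text does not support that: fatal and life-threatening events can be compared.
- **The hospitalisation sentence does not say only.** Site PIs record adverse events with no limit by arm or time, and the CSRI asks about hospital use in both arms. It would be wrong to say that admissions outside the course go unrecorded. What stands is that neither source is stated to reach the IDMC.
- **Details may sit elsewhere.** National requirements govern reporting and may be broader, and a journal article condenses the full protocol. This has some force, but the article does more than omit a definition: it states a narrow one. Separate national rules in three countries also do not by themselves give one common definition.
- **During the intervention may be meant as a calendar window**, running alongside the course for both arms. That is a possible reading, but it is not stated, and it would still end before the 6-month follow-up.
- **Facilitators are not named as a reporting route.** This is correct. Uneven detection is a possibility raised by the extra contact, not something that the plan prescribes.
- **This is a low-risk, non-pharmacological trial**, and lighter reporting is a declared choice. That limits how much extra logging is reasonable. It does not explain why the rule should be undefined for one arm.

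Two further inferences should be resisted. One is that most serious events never reach the IDMC; the documents give no event rates, so no such share can be stated. The other is that the committee's independence is compromised because "There will also be a trial representative on the committee". The article does not say that this person votes, attends closed sessions or sees data by arm. Those matters belong in a committee charter, and no flaw is stated.

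**Conclusion.** The concern holds for hospitalisations that are not life-threatening. The article defines serious events too narrowly to include them, ties the only explicit hospitalisation rule to a period that TAU does not literally have, and states no route by which they reach the IDMC equally in both arms through follow-up 2. The explicit rule covers 24% to 28% of follow-up, given a lag of 0 to 6 weeks and a first follow-up at the end of the course. The CSRI raises coverage of hospital use to about 62% to 66% in both arms, but it is collected for service use and costs, not for safety review.

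The number of admissions affected cannot be given, because the documents contain no rate. The consequence is an incomplete, and possibly uneven, safety comparison of admissions. The comparison of fatal and life-threatening events is not affected. The point deserves correction, in proportion to a low-risk trial.

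**What to change.** Reconcile *Assessment and management of risk* with *Safety reports of serious adverse events (SAE)* as follows.

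1. State that hospitalisations are recorded from randomisation to follow-up 2 in both arms, whether or not they are life-threatening.
2. Ascertain them in the same way in both arms: the blinded assessor asks at follow-up 1 and follow-up 2, using the CSRI hospital-use items. Extend recall at follow-up 2 to all time since follow-up 1. If more than 3 weeks can pass between randomisation and course start, extend recall at follow-up 1 back to randomisation as well. Ask for admission dates, so that the standard 3-month window for costs can still be extracted.
3. Tabulate hospitalisations by arm in the 6-monthly IDMC report.

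The cost is one extended recall question (two if the lag is long), one table and slightly more event logging. Existing CSRI data alone would not be enough, because the standard recall misses about the first 13 weeks after follow-up 1. Longer recall may be less accurate, but it would apply to both arms alike. *Trial status* says recruitment had not opened at submission, so at that stage the change could be made before any data were collected.
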